**Table 3. Reoperation cutoff values for study termination.**

| $n^1$ | $CI_{up}^2$ |
|-------|-------------|
| 10    | 4           |
| 20    | 5           |
| 30    | 7           |
| 40    | 8           |
| 50    | 10          |

Number of recruited patients in the treatment arm. Corresponding calculated  $CI_{up}$  number of cases for the complication "reoperation" [1]. If the respective case number exceeds the calculated  $CI_{up}$  number, the study will be terminated.

[figure not shown]

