**Table 1. Incidence of know complications for neoadjuvant CRT following surgical resection.**

| Complications (n=128)          | Percentage (%) | Citation |
|--------------------------------|----------------|----------|
| Any postoperative complication | 39             | [1]      |
| Any surgical complication      | 23             | [1]      |
| Reoperation                    | 7              | [1]      |

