### Statistical methodology

Interim analyses will be performed after every 10 patients from the treatment arm: Reoperation numbers will be determined and the 95% CI compared to historically known and published ratios [1].

95% CI (Exact binomial test) for complication percentages between 5% and 40% in 2.5 steps and expected case numbers are calculated for n=30 (control group) and n=50 (treatment group) patients (Table 2).

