#### 11.4.6 Interim analysis

Interim analyses will be performed after every 10 patients from the treatment arm to assess the reoperation complication rate compared to CI of known ratios. If the 95% CI upper limit gets exceeded at any time, the study will be terminated.

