#### 11.4.7 Software program

All statistical analyses will be computed with R version 3.6.1 [43]. The R-package “binom 3.6.0” using the “*binom.test*” function (exact binomial test). Rounding to the concrete case numbers was performed with an own rounding function implementing the “round half up” method, not the round to even method usually used from the R round-function.

[figure not shown]

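### Table 3's reoperation stopping limits are confidence limits around an imagined result, not limits on the counts compatible with the published 7%, so the rule rarely stops the trial when reoperations are raised

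*Protocol*

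**What the plan says.** Table 1 gives a published reoperation rate of 7% from a series of 128 patients. The synopsis, under Statistical methodology, provides for a look after every 10 treatment-arm patients: "Reoperation numbers will be determined and the 95% CI compared to historically known and published ratios". Table 3, "Reoperation cutoff values for study termination", then lists one limit per look (4, 5, 7, 8, 10), and its footnote ends the study only if the count is above the limit.

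Section 11.4.6 describes the looks as made "to assess the reoperation complication rate compared to CI of known ratios", and adds: "If the 95% CI upper limit gets exceeded at any time, the study will be terminated". The termination criteria at the end of that section point to Table 3.

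For the final analysis, the synopsis text after Table 2 compares the count of each complication with tabulated lower and upper borders. The treatment is considered safe if the counts in both groups lie between them, and unsafe for a complication whose treatment-arm count lies above the upper border. Section 11.4.7 names the exact binomial method and states: "Rounding to the concrete case numbers was performed with an own rounding function", with halves rounded up.

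**The concern.** A stopping limit for reoperations should mark the count above which the data no longer fit the reference rate. Table 3 answers a different question: if exactly the expected number had been observed, how high could the true rate be? That value, multiplied by n, lies well above the range of counts that a true 7% would produce.

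Safety is the primary objective, and Table 3 is the protocol's only numerical stopping rule. If its limits are too wide for what they are taken to be, the trial continues through counts that already exclude 7%, and the same construction in Table 2 carries over to the final assessment of reoperation. In addition, the synopsis and section 11.4.6 do not clearly describe the same comparison.

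**Working it through.** **Inputs.** Reference rate 7% (Table 1). Looks at n = 10, 20, 30, 40, 50, and termination only when the count exceeds the limit (Table 3 and its footnote). Exact binomial interval and round-half-up (section 11.4.7).

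**Step 1: reproduce Table 3.** Let x = 0.07n, rounded half up. Take the upper two-sided 95% Clopper-Pearson limit for x/n, multiply by n, and round half up.

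| n | 0.07n | x | upper limit × n | rounded | Table 3 |
|---|---|---|---|---|---|
| 10 | 0.7 | 1 | 4.45 | 4 | 4 |
| 20 | 1.4 | 1 | 4.97 | 5 | 5 |
| 30 | 2.1 | 2 | 6.62 | 7 | 7 |
| 40 | 2.8 | 3 | 8.15 | 8 | 8 |
| 50 | 3.5 | 4 | 9.62 | 10 | 10 |

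All five limits are reproduced. The same recipe gives every interval border in Table 2.

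**Step 2: counts compatible with 7%.** The smallest c with P(X > c) ≤ 0.025 for X ~ Bin(n, 0.07) is 3, 4, 5, 6, 7. Equivalently, the lower exact 95% limit of the observed proportion first exceeds 7% at 4/10 (12.2%), 5/20 (8.7%), 6/30 (7.7%), 7/40 (7.3%) and 8/50 (7.2%). Table 3 first stops at 5, 6, 8, 9 and 11.

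**Step 3: chance of exceeding Table 3 at a true 7%.** P(X > limit) = 0.03%, 0.19%, 0.08%, 0.15% and 0.06% at the five looks.

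**Step 4: cumulative stopping probability over five looks.** This is the exact convolution of five groups of 10, carrying forward only paths that have not stopped, and it assumes that all n patients are operated.

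| True rate | Table 3 | Observed 95% CI against 7% |
|---|---|---|
| 7% | 0.35% | 3.8% |
| 10% | 2.6% | 16% |
| 12.9% | 9.6% | 37% |
| 14% (double) | 14% | 46% |
| 21% (triple) | 57% | 87% |

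**Step 5: final assessment.** Table 2 has no 7% row. Its 7.5% row at n=50 has borders 1 and 10, the upper one equal to Table 3's last limit. Against that row:

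- 8/50: exact 95% CI 7.2% to 29.1%, inside the borders.
- 9/50: 8.6% to 31.4%, inside the borders.
- 10/50: 10.0% to 33.7%, on the border and therefore not above it. Whether being between the borders includes the border itself is not stated.

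All three intervals exclude a fixed 7%.

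**Step 6: allow for uncertainty in the reference.** The protocol treats 7% as known. Assuming it stands for 9/128 (0.07 × 128 = 8.96; exact 95% CI 3.3% to 12.9%), two-sided Fisher tests against 8, 9 and 10 of 50 give p = 0.088, 0.049 and 0.027.

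**The case against.** Nothing in Table 3 is miscalculated: the limits follow from the declared method and rounding rule. The fault lies in which quantity was calculated, so this objection does not remove it.

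A reader might infer that the protocol contains two rival stopping rules. The documents do not support that. There is one set of limits, and the synopsis text after Table 2, Table 3 and section 11.4.6 all apply it as a fixed border around the reference. The synopsis sentence on the looks does not say whose interval is meant and sets no termination criterion. What stands is an ambiguity.

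A reader might also infer that the rule breaks a promised 2.5% per look. No such error rate is stated; 95% labels a confidence interval. Limits stricter than 2.5% could be deliberate with five looks, but the protocol does not say so.

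Nor does it follow that 8 to 10 reoperations in 50 would by themselves have the treatment declared safe. That verdict also needs the control arm within its borders and depends on the other complications. Moreover, 8/50 excludes 7% only if 7% is taken as fixed.

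Finally, Table 3 is not the only safeguard. Section 7.1.7 allows termination for an unacceptable risk-benefit ratio. That is a judgement and does not repair the table.

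**Conclusion.** The point holds as a fault of method. Table 3 uses an interval for a rate, given an imagined result, as a limit on counts. It leaves the trial running in 86% of cases (100% − 14%) when the reoperation rate is double the reference and in 43% (100% − 57%) when it is triple. The observed-interval comparison would leave it running in 54% and 13%.

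The figures assume that every counted patient is operated. Table 3's footnote counts recruited patients, and any not yet operated make crossing less likely. They also take 7% as fixed, as the protocol does. With 9/128 as the assumed reference, 8/50 is no longer significant and 9/50 is borderline, while 10/50 still differs. The finding about how Table 3 was built rests on neither assumption. Because it concerns the numerical termination rule of a trial whose primary objective is safety, it should be corrected.

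**What to change.** Reconcile the synopsis (the sentence on the looks, the decision text after Table 2, and Table 3) and section 11.4.6, including its termination criteria, to one stated comparison. Recompute Table 3, and the Table 2 borders used for reoperation, from it, and add a row or rule for the 7% reference.

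- If a comparison with 7% at the 95% level is meant, derive the limits from the binomial distribution at the reference rate (3, 4, 5, 6, 7, terminating when exceeded). This is the same as asking whether the observed lower 95% limit is above 7%.
- If the wider limits are intended, say so, give the reason, and do not present them as a 95% limit on expected counts.

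In either case, state the cumulative stopping probability at 7% and at raised rates.

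The editing cost is small: one recomputed table, the matching borders and aligned wording. The price of binomial limits is more stopping near the reference: 3.8% at a true 7%, 16% at 10% and 37% at 12.9%, against 0.35%, 2.6% and 9.6% for Table 3. The sponsor should weigh that trade-off openly; which limit is clinically right is not decided here.

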### Sample size calculation

No formal sample size calculation was performed for this safety, tolerability and feasibility phase 2 study.

The 30:50 randomization ratio is a trade-off between having as much as possible patients in the treatment arm and enough patients in the control arm (standard of care treatment complication rates are well known).

The sample size of 80 is defined by the expected patient numbers available in the planned and financed duration time of the study (based on incidence, inclusion criteria and anticipated patient consent ratios). The primary objective (safety) can be compared to known and published values [1]. A doubling (100% increase) of any surgical complication (23% x 2 = 46%) can be excluded with 49 patients (Power=0.90;  $\alpha$ =0.05).

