## 8.3 Surgery

Patients will be operated about 10-12 weeks post CRT. Surgical options included standard total mesorectal excision (TME) or extended TME (*i.e.* TME with adjacent visceral resection) with or without sphincter preservation (abdominoperineal excision; APE) according to a standardized technique [34][3]. Patients will receive either a minimal invasive (laparoscopic, laparoscopic-assisted or robotic) or an open approach, depending on the perioperative circumstances (*i.e.* body constitution and cardiopulmonary fitness of the patient) and the surgeon's choice and expertise.

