### 11.4 Statistical analysis plan (SAP)

#### 11.4.1 Missing, unused and spurious data

In general, every effort shall be made by site staff to avoid the occurrence of missing data. However, in case data is not recorded, this must be clearly stated in the eCRF. The statistical analysis will also report the frequency of missing values.

Patients with missing data for a specific side effect will be excluded from the evaluation of this side effect. Missing data for secondary objectives will be imputed with values estimated by the predictive mean matching method using R-package “mice” (version 2.30), if appropriate.

[figure not shown]

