#### 11.4.2 Primary endpoint analysis

Safety and tolerability will be assessed by comparing case numbers for any complication in the treatment arm (n=50) with the calculated 95% upper CI numbers of the calculated percentage of expected numbers of current standard therapy (Table 2). Case numbers in the control arm (n=30) will be used to validate expected numbers from current standard therapy (*i.e.* will be compared to the corresponding 95% CI lower and upper borders).

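### Table 3 reads its reoperation stopping limits at recruited patients, although only operated patients can have the event, so early looks have little chance to stop the trial

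*Protocol*

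**What the plan says.** The synopsis (Statistical methodology, Table 3) gives upper case limits for reoperation of 4, 5, 7, 8 and 10 at n = 10, 20, 30, 40 and 50. Footnote 1 defines n as "Number of recruited patients in the treatment arm". Footnote 2 sets the rule: "If the respective case number exceeds the calculated" upper limit, the study ends. Section 11.4.6 says "Interim analyses will be performed after every 10 patients from the treatment arm to assess the reoperation complication rate". The synopsis text before Table 3 and the termination criteria under 11.4.6 likewise speak only of every 10 patients of the treatment group.

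On timing, section 8.3 states "Patients will be operated about 10-12 weeks post CRT". Section 7.1.5 gives 5 weeks of CRT before that interval, and Table 4 puts surgery at weeks 15 to 17 and the end-of-study visit at week 20.

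For the final assessment, section 7.1.6 replaces only patients who leave before the first treatment cycle and keeps later drop-outs in the sample size. Section 11.4.1 states "Patients with missing data for a specific side effect will be excluded from the evaluation of this side effect". Section 11.4.2 and the synopsis compare case counts with limits calculated for 50 treatment-arm and 30 control patients.

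**The concern.** The limits are binomial bounds for n patients who could each have been reoperated. If n counts recruits, the latest of them have not reached surgery and contribute no events, while the limit is read as if they could. The error always runs towards not stopping and is largest at the first looks, where stopping would spare most patients. Table 3 is the only numerical stopping rule in the protocol; section 7.1.7 adds qualitative criteria only.

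The final rule has the same structure. If evaluable patients fall below 50 while the limit stays put, more excess risk passes as acceptable.

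**Working it through.** **Reproducing Table 3.** Expected cases are 0.07 × n, rounded half up; the limit is the two-sided 95% exact upper bound times n, rounded half up (method from section 11.4.7, 7% from Table 1). The unrounded limits are 4.45, 4.97, 6.62, 8.15 and 9.62, which give 4, 5, 7, 8 and 10. All five match.

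**Patients operated at a look held at recruitment.** The planned dates (1Q 2020 to 2Q 2022) allow 24 to 30 months of accrual. Assume even accrual of 50 treatment-arm patients:
- Gap between patients = months × 4.35 weeks / 50, which is 2.09, 2.35 and 2.61 weeks for 24, 27 and 30 months.
- Patients awaiting surgery = lag / gap. The extremes are 15/2.61 = 5.7 and 17/2.09 = 8.1; the middle is about 7.
- Operated at the 10th recruit = 10 − 8.1 = 1.9 up to 10 − 5.7 = 4.3, so 1 to 4 whole patients.

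Stopping needs at least 5 reoperated patients, so its probability is 0 in this range. Five operated by then needs 5 × gap ≥ 15 weeks, a gap of 3.0 weeks, or 150 weeks (about 34 months) for 50 patients. That is slower than planned.

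**The first look with all 10 operated.** P(X > 4 | n = 10) is 0.7% at a true 14% (twice the reference) and 4.0% at 21% (three times).

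**Cumulative chance of stopping.** This is an exact recursion. With f_k(x) the probability of x cases at look k without an earlier stop, f_k(x) = Σ f_(k−1)(y) × Bin(x − y; n_k − n_(k−1), p) over y ≤ c_(k−1). The stop probability at look k is the sum of f_k(x) over x > c_k, with c = 4, 5, 7, 8.

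| True rate | n operated at looks 1–4 | Look 1 | By look 2 | By look 3 | By look 4 |
|---|---|---|---|---|---|
| 14% | 10/20/30/40 | 0.7% | 5% | 7% | 12% |
| 14% | 3/13/23/33 | 0% | 0.5% | 1% | 4% |
| 21% | 10/20/30/40 | 4.0% | 23% | 34% | 50% |
| 21% | 3/13/23/33 | 0% | 4% | 10% | 25% |

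Using 1/11/21/31 or 4/14/24/34 operated instead, the same recursion gives 19% to 29% by look 4 at a true 21%, and 2% to 5% at 14%.

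**Final limits by the protocol's own method.**
- Reoperation: 10 at 50 patients, 8 at 45. Part of this step is rounding: 0.07 × 50 = 3.5 rounds to 4, while 0.07 × 49 = 3.43 rounds to 3. At 45 operated and a true 21%, P(more than 8) is 62% and P(more than 10) is 34%.
- Surgical complications: the 22.5% row of Table 2, nearest to the published 23%, gives 18. Computed at 23%, the limit is 18 for 46 to 49 operated, 17 at 45 and 15 at 40. At 50 it is 19, so the tabled 18 is then slightly strict.

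**The stated power.** The protocol says "A doubling (100% increase) of any surgical complication (23% x 2 = 46%) can be excluded with 49 patients", with power 0.90. Comparing 46% with 23% in the 128 historical patients of Table 1, one-sided 5%, gives 0.903 at 49, the smallest n reaching 0.90. The protocol does not name the method; this one reproduces its figure. It gives 0.89 at 45 and 0.86 at 40.

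**The case against.** The running text does not say that a look is held on the day the tenth patient is recruited. One can read n as a cohort label, with the look held once that cohort's outcomes exist, and section 11.4.6 also speaks of the limit being exceeded at any time. A reader might infer that the first look can never stop the trial. The documents do not support that as a fact: it depends on looks held at recruitment and on even accrual at the planned pace. The first look is also nearly inert because of its limit of 4, so correcting the denominator gains little there. What remains is that the only definition of n given is recruitment, and nothing elsewhere corrects it.

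A comparison over all five looks, 33% against 57% at a true 21%, would also mislead, because it stops at 43 operated in one scenario and 50 in the other. Adding the end-of-study comparison on all 50 raises the 33% to about 50%. A crossing at that stage protects nobody still to be treated, so the comparison through look 4 is the fairer one.

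Comparing by look number also flatters the correction, because operated-based looks come later. By recruits: with 7 pending, the fourth operated-based look falls at about 47 recruits and has a 50% cumulative chance at a true 21%. The recruitment-based rule has reached 33% at 50 recruits. The gap narrows but stays.

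On the final rule, a reader might infer that the limit will be too lenient. With all 50 operated it is not, and no non-operation rate is given; 45 and 40 are illustrations. Section 11.4.1 speaks of missing data for a side effect and does not say how a patient without surgery is classed. Nor do the documents support a large loss of the stated power.

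**Conclusion.** The point holds for the interim rule. Table 3 states a denominator that includes patients who cannot yet have the event. With looks at recruitment and even accrual over 24 to 30 months, the chance of stopping by the fourth look roughly halves at a true 21% (25% against 50%) and falls to about a third at 14% (4% against 12%). If the looks were always meant to wait for surgery, the limits are right as they stand and only the footnote and trigger wording are wrong; they need correcting either way.

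The final-limit point is conditional. It matters to the extent that treatment-arm patients are not operated or evaluable, and its size cannot be fixed from the protocol.

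**What to change.** - In the Table 3 footnote, the synopsis text before it, section 11.4.6 and its termination criteria, define n as treatment-arm patients operated and assessed to the postoperative visit. Hold the looks when that number reaches 10, 20, 30, 40 and 50.
- Alternatively, keep the calendar of looks and compute each limit for the number operated. For 3/13/23/33/43 operated the protocol's method gives 2/5/6/7/8. By the recursion above, the chance of stopping by look 4 is then 40% at a true 21%, 9% at 14% and 0.2% at the reference 7%.
- In section 11.4.2 and the matching synopsis text, replace the limits fixed at 50 and 30 by limits for the number operated and evaluable in each arm, and say how patients without surgery are counted.
- State that the 0.90 power assumes 49 evaluable treatment-arm patients.

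The cost is wording and a short lookup table. The real downside of the first option is delay: each look comes about 7 recruits later, or 8 to 9 (20/2.35 = 8.5) if the week-20 visit is required. The protocol should say so.

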### 3 LIST OF ABBREVIATIONS

|          |                                                            |
|----------|------------------------------------------------------------|
| AE       | Adverse Event                                              |
| BRAF     | V-raf murine sarcoma viral oncogene homolog B1             |
| CI       | Confidence Interval                                        |
| CRC      | colorectal cancer                                          |
| CRO      | Clinical Research Organization                             |
| CRT      | Chemoradiotherapy                                          |
| CSR      | Clinical Study Report                                      |
| CT       | Computed tomography                                        |
| CTCAE    | Common Terminology Criteria of Adverse Events              |
| CTLA-4   | Cytotoxic T-lymphocyte-associated protein 4                |
| DSUR     | Development Safety Update Report                           |
| ECG      | Electrocardiography                                        |
| ECOG     | Eastern Cooperative Oncology Group                         |
| eCRF     | Electronic Case Report Form                                |
| EORCT    | European Organization for Research and Treatment of Cancer |
| EOS      | End of Study                                               |
| EOSV     | End of Study Visit                                         |
| ESMO     | European Society for Medical Oncology                      |
| EU       | European Union                                             |
| EudraCT  | European Union Drug Regulating Authorities Clinical Trials |
| FDR      | False discovery rate                                       |
| GCP      | Good Clinical Practice                                     |
| Gy       | Gray                                                       |
| HBV      | Hepatitis B Virus                                          |
| HIV      | Human Immunodeficiency Virus                               |
| HVC      | Hepatitis C Virus                                          |
| ICH      | International Conference on Harmonization                  |
| ICI      | Immune checkpoint inhibitors                               |
| IEC      | Independent Ethics Committee                               |
| IMP      | Investigational Medicinal Product                          |
| imRECIST | immune-modified RECIST                                     |
| IRB      | Institutional Review Board                                 |
| iRECIST  | Immune RECIST                                              |
| irRC     | Immune-related response criteria                           |
| ISF      | Investigator Site File                                     |
| IV       | Intravenous                                                |
| KRAS     | Kirsten rat sarcoma viral oncogene homolog                 |
| LARC     | locally advanced rectal cancer                             |
| LLT      | Lower level terms                                          |
| MRI      | Magnetic resonance imaging                                 |

[figure not shown]

|            |                                                                        |
|------------|------------------------------------------------------------------------|
| MSI        | Microsatellite instable                                                |
| MSS        | Microsatellite stable                                                  |
| N.A.       | Not Applicable                                                         |
| NCI        | National Cancer Institute                                              |
| PBMCs      | Peripheral blood mononuclear cells                                     |
| PD-1       | Programmed cell death protein 1                                        |
| PD-L1      | Programmed death-ligand 1                                              |
| PD-L2      | Programmed death-ligand 2                                              |
| PET        | Positron-emission tomography                                           |
| PIK3CA     | Phosphatidylinositol-4,5-bisphosphate 3-kinase catalytic subunit alpha |
| PO         | Per os                                                                 |
| PTEN       | Phosphatase and tensin homolog                                         |
| QLG        | Quality of Life Group                                                  |
| RECIST 1.1 | Response evaluation criteria in solid tumors 1.1                       |
| RFS        | Recurrent-free survival                                                |
| SAE        | Serious Adverse Event                                                  |
| SAP        | Statistical analysis plan                                              |
| SAR        | Serious Adverse Reaction                                               |
| SOP        | Standard Operating Procedure                                           |
| SUSAR      | Suspected Unexpected Serious Adverse Reaction                          |
| TIME       | Tumor immune microenvironment                                          |
| TMB        | Tumor mutational burden                                                |
| TP53       | Tumor protein p53                                                      |
| Treg       | Regulatory T cells                                                     |
| TRG        | Tumor Regression Grade                                                 |

[figure not shown]

